#### Blinding/Masking

The study coordinator will generate the allocation sequence, and two researchers will administer the nicotine gum, but they will be blind with regard to the dosage. Two different researchers will conduct the statistical analyses. They will be unaware of the condition analyzed. The participants will be interviewed at the end of the study (by the selected researchers) to determine if the blinding was broken. If the blind is broken, additional analyses without the unblinded cases will be conducted to test the effects of unblinding. Some participants might be able to tell which dose they received on the basis of physical alterations; however, malaise will be assessed at the end of each period session.

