### General Study Design

The ENIGMA-Vis is designed to be a randomized, double-blind, and placebo-controlled three-period trial (RBR-46tjy3) to investigate the effects of nicotine gum administration on vision. The diagram is shown in Table 1. This trial comprises three main gum administrations (placebo, 2-mg, and 4-mg doses). Participants will be followed up at 4 weeks, and the assessments will be performed in week 0 (baseline) to week 3. Female participants will be tested outside their luteal phase.

**TABLE 1 T1:** Measures by timepoint for the schedule of enrolment, interventions, and assessments.

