### Safety, Dropouts, and Adherence

The nicotine gum administration can act in the area postrema (chemoreceptor zone). This structure is involved in the emetic mechanisms and can cause nausea (Changeux, 2018). Because nicotine is a vasoactive substance, some participants may report a headache, giddiness, and sweating. Other adverse events can be sore throat due to menthol. Nevertheless, as reported by Naser et al. (2011) and Varghese et al. (2011), the nicotine gum administration is safe, and the adverse events are not related to all participants.

The participants will be asked at the end of each session whether they had adverse events such as “tingling,” “nausea,” and “headache” among others and asked about the intensity (1 = none to 4 = strong) and whether this effect could be related to the nicotine gum. Dropouts will be considered if the individual (1) misses two consecutive visits during the study; (2) does not complete all of the nicotine gum administration; (3) presents any severe adverse events during the trial; and (4) expresses the wish to stop participation for any reason. Retention strategies will be employed to ensure adherence and reduce dropouts, such as accessibility of the investigators, flexibility with the visit scheduling (not exceeding 1 week between measures), transportation to our laboratory, and expense reimbursement.

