**FIGURE 2 F2:**
[figure not shown]
Illustration of the procedure used in the randomized clinical trial. The black square symbol represents the testing procedure (i.e., task). A washout period of one week between periods will be used.

After 5 min of chewing, the participants will dark-adapt for 10 min. Next, they will be light-adapt to the corresponding display for 3 min. During these 3 min, they will be familiarized with the corresponding test using suprathreshold stimuli. This procedure will ensure that all the participants are in the same photopic adaptation state and understand the instructions. When the testing begins, 18 min will have passed since they started chewing the gum, and they will dispose of the gum.

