#### Additional Analyses

Missing data will be considered as random (MAR), and the maximum likelihood estimation (MLE) will be used. Under the MAR assumption, MLE appears to represent an interesting and unbiased approach, even to continuous and discrete variables (Dziura et al., 2013). Nevertheless, we will analyze individuals with missing data and without missing data. We expect to have no more than 5% of missing data and differences between with and without missing data.

Exploratory analysis to investigate whether sex, age, and level of education are predictors of response will be performed. Multivariate regression analysis will be used to investigate whether demographics would be predictors of the effects of nicotine gum. We will also conduct a separate regression analysis to investigate whether or not cotinine serum levels would be predictors of visual performance. These variables can be also used as mediators of the interaction between conditions.

Finally, adverse events will be presented as percentages in each condition. Cochran’s *Q* test will be conducted to investigate the effectiveness of the masking and blinding (on this analysis, we will calculate the ratio between errors and correct responses regarding the condition in which the participant believed was applied).

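### Blinding is checked once, at the end of the study, so answers about sessions 1 and 2 come after the gums can be compared and do not show what participants believed while being tested

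*Protocol article*

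**What the plan says.** The protocol article fixes the timing of the blinding question under Blinding/Masking: "The participants will be interviewed at the end of the study (by the selected researchers) to determine if the blinding was broken". Should that interview show a broken blind, the section plans further analyses that leave out the unblinded cases. It also concedes that bodily sensations may tell some participants which dose they had, and adds that "malaise will be assessed at the end of each period session".

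Under Additional Analyses, Cochran's Q is planned to assess masking, and "we will calculate the ratio between errors and correct responses regarding the condition in which the participant believed was applied".

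Safety, Dropouts, and Adherence describes what is asked at each visit: "The participants will be asked at the end of each session whether they had adverse events", how intense they were, and "whether this effect could be related to the nicotine gum". It does not ask which gum the participant thinks was given.

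The design is within-subject. General Study Design says "This trial comprises three main gum administrations (placebo, 2-mg, and 4-mg doses", and the Figure 2 caption says "A washout period of one week between periods will be used". Table 1 places the vision measures in weeks 1, 2 and 3 and again at a close-out headed 40 weeks.

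**The concern.** Both uses of the blinding information need to know what a participant believed during a particular vision test. The sensitivity analysis asks whether a dose effect survives once people who knew their gum are removed. Cochran's Q takes one binary result per participant and condition, so it needs a belief for each of the three sessions.

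A single interview after all three gums gives something else: a reconstruction. A participant who had no idea in session 1 may name that gum correctly at the end because a later one felt stronger. That session would be scored as unblinded although it was tested blind. Conversely, a participant who was sure, and right, in session 1 may forget or revise that belief after a later session, and truly unblinded data would be kept.

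This matters here because the participants are never-smokers, the protocol expects sensations such as nausea and headache, the hypothesis is directional (a higher dose gives better vision), and the outcomes are behavioural responses. If a dose effect appears, the natural question is whether expectation contributed to it, and the plan would answer from beliefs recorded at the wrong time.

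**Working it through.** The protocol gives no figure for this point, so there is none to reproduce. The check compares the stated timings, works out the recall intervals, and then separates what depends on timing from what does not.

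**Timings side by side**

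| Item | When recorded | Names the gum? |
|---|---|---|
| Blinding interview (Blinding/Masking) | End of the study | Presumably |
| Malaise (Blinding/Masking) | End of each session | No |
| Adverse events, intensity, possible relation to nicotine gum (Safety, Dropouts, and Adherence) | End of each session | No; does not separate the three conditions |
| Believed condition for Cochran's Q (Additional Analyses) | Not stated | Yes |

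The Blinding/Masking section uses two different timings within one paragraph, so the end-of-study timing is stated and distinct. The interview is the only stated source for deciding who was unblinded. It appears to be the source for Cochran's Q as well, but Additional Analyses does not say so.

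**Recall interval**

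Inputs: sessions in weeks 1, 2 and 3 (Table 1), one week apart (Figure 2 caption). The interview week is not given, so three readings of the end of the study are shown. The second comes from General Study Design ("Participants will be followed up at 4 weeks, and the assessments will be performed in week 0 (baseline) to week 3"), counting the 4 weeks from week 0. The third is Table 1's close-out heading.

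Interval in days = (interview week − session week) × 7.

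| Interview taken at | Session 1 | Session 2 | Session 3 |
|---|---|---|---|
| Directly after session 3 (week 3) | (3−1)×7 = 14 | (3−2)×7 = 7 | (3−3)×7 = 0 |
| 4-week follow-up | (4−1)×7 = 21 | (4−2)×7 = 14 | (4−3)×7 = 7 |
| 40-week close-out | (40−1)×7 = 273 | (40−2)×7 = 266 | (40−3)×7 = 259 |

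The 14 and 7 days are thus the shortest of the three readings. They assume exact weekly spacing. The safety section allows flexible scheduling within a one-week limit between measures, so the true values are approximate.

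**What hindsight adds**

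Assume participants know that each gum comes once (the article does not say whether they are told). Asked at the end of session 1, a participant with no clue has a 1/3 chance of naming the gum. Asked after session 3, having recognised one later gum, the chance for session 1 is 1/2. Having recognised both later gums, it is 1. None of that knowledge existed during the session 1 test.

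Elimination in the other direction is different. Someone who recognised the first two gums really does know the third while being tested on it, and scoring that session as unblinded is right. A guess at the end of each session keeps the two cases apart; a single final interview cannot.

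**The case against.** The strongest points on the other side are these.

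- **The article is condensed.** The full protocol may contain a session-level guess, and Additional Analyses does not say when the believed condition is recorded. This stands as far as Cochran's Q is concerned, so the link is put only as apparent. It does not remove the point, because the article states the timing of the interview that decides whether blinding was broken.
- **There is some real-time information.** Malaise and adverse events are asked about at every session, including whether an effect could be related to nicotine gum. This is a partial signal of belief at the time. It does not distinguish placebo, 2 mg and 4 mg, depends on an effect being reported, and is not linked to the blinding analysis.
- **Asking early may prompt participants to think about the gum later.** This is a fair trade-off, but a small addition, since the session-end questions already raise a possible relation to nicotine.
- **The consequence is limited.** The placebo is matched for taste, texture and tingling, the vision tests are forced-choice staircases with catch trials, and the primary MANOVA does not use the guesses. This stands and limits the weight of the point.

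A reader might also infer that late questioning multiplies the number of participants who appear fully unblinded by chance: 1/3! = 1/6 for a joint ordering of the gums, against (1/3)³ = 1/27 for separate guesses, or about 8 against 2 of 50. The documents do not support this. A participant asked at each session who never repeats a guess is fully correct by chance with probability 1/3 × 1/2 × 1 = 1/6, so the contrast comes from knowing that each gum occurs once, not from when the question is asked. The chance rate for each condition is 1/3 either way, so it does not inflate the rates Cochran's Q compares. Nor does the protocol define an unblinded case as three correct guesses.

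**Conclusion.** The point holds as a weakness in when belief is recorded. Answers about sessions 1 and 2 are given after the gums can be compared, and at least about 14 and 7 days later if the interview directly follows session 3 and sessions are weekly. They cannot show what the participant believed during those tests. They nevertheless determine which cases are left out of the sensitivity analysis, and apparently supply Cochran's Q. The direction and amount of misclassification cannot be computed from the document: blind sessions may be discarded and unblinded ones kept.

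It would go too far to conclude that the trial's main comparison is invalid or that blinding will fail. The primary MANOVA is untouched, and nothing in the article shows how often participants will recognise their gum. What is at stake is whether the blinding check and its sensitivity analysis can bear the interpretation planned for them. The change is cheap, and beliefs held at the time cannot be recovered once sessions are over.

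**What to change.** At the end of each session, after the vision test and together with the existing adverse-event questions, record which gum the participant believes was given: placebo, 2 mg, 4 mg or don't know. Do not reveal whether the answer is correct. State under Additional Analyses that these session-level answers feed the blinding analysis, and under Blinding/Masking that they define the sessions left out of the sensitivity analysis. Keep the end-of-study interview as descriptive only.

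Recall is then about 0 days for all three sessions, and the session 1 answer is given before any comparison gum has been tried.

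Cost: one extra question at each of three session-end interviews that are already planned. The downside is slightly more attention to the gum in sessions 2 and 3; placing the question after the test and withholding correctness limit this.

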### Safety, Dropouts, and Adherence

The nicotine gum administration can act in the area postrema (chemoreceptor zone). This structure is involved in the emetic mechanisms and can cause nausea (Changeux, 2018). Because nicotine is a vasoactive substance, some participants may report a headache, giddiness, and sweating. Other adverse events can be sore throat due to menthol. Nevertheless, as reported by Naser et al. (2011) and Varghese et al. (2011), the nicotine gum administration is safe, and the adverse events are not related to all participants.

The participants will be asked at the end of each session whether they had adverse events such as “tingling,” “nausea,” and “headache” among others and asked about the intensity (1 = none to 4 = strong) and whether this effect could be related to the nicotine gum. Dropouts will be considered if the individual (1) misses two consecutive visits during the study; (2) does not complete all of the nicotine gum administration; (3) presents any severe adverse events during the trial; and (4) expresses the wish to stop participation for any reason. Retention strategies will be employed to ensure adherence and reduce dropouts, such as accessibility of the investigators, flexibility with the visit scheduling (not exceeding 1 week between measures), transportation to our laboratory, and expense reimbursement.

#### Intervention

This trial will follow the assumptions proposed by Russell et al. (1976), where the average peak of plasma nicotine is expected to occur between 15 and 45 min after the beginning of the chewing. The tests will be performed in this time window. Two dosages (2-mg and 4-mg) of nicotine gum (Nicorette, GlaxoSmithKline, and Wales) and one placebo gum, with the same taste, texture, and similarity to the nicotine gum (e.g., levomenthol, mint oil, and winter-fresh essence; producing tingling on the gums, the same sensations produced by active nicotine gum) will be used in this study. The choice for using these dosages (2-mg and 4-mg) is based on the commercially available options for the icy mint option. In addition, we opted to pick the two lowest dosages initially to minimize side effects. The participants will be asked to gently chew the gum for 15 min, while maintaining the same speed and intensity before the tests are performed (Figure 2). We will instruct them to minimize the possibility of bias although, to our knowledge, no study has reported an association between speed or intensity of chewing and the amount of nicotine absorbed (for details, see Benowitz et al., 2009). During this time, the participants will be allowed to read recreational material, but they will not be allowed to text or read emails. Members of the research team will monitor the participant to ensure that they chew according to instructions.

**FIGURE 2 F2:**
[figure not shown]
Illustration of the procedure used in the randomized clinical trial. The black square symbol represents the testing procedure (i.e., task). A washout period of one week between periods will be used.

After 5 min of chewing, the participants will dark-adapt for 10 min. Next, they will be light-adapt to the corresponding display for 3 min. During these 3 min, they will be familiarized with the corresponding test using suprathreshold stimuli. This procedure will ensure that all the participants are in the same photopic adaptation state and understand the instructions. When the testing begins, 18 min will have passed since they started chewing the gum, and they will dispose of the gum.

### Sample Size

There were no previous reports of sample size estimation from a meta-analysis or equivalent study. Because of the lack of this information, the effect size will be estimated using the minimal meaningful effect size (0.05) (Sullivan and Feinn, 2012) and the power will be used considering a common value in clinical trials (Charan and Biswas, 2013). Considering a two-sided test with an alpha value of 0.01 (or 0.02 for a one-sided test) and a power of 85% (or 0.85), the sample size would require at least 42 individuals to complete the three periods for each study. As this trial is a single group model, with an anticipated 20% attrition rate, our main intention is to enroll 50 individuals for each study (Study 1, *N* = 50; Study 2, *N* = 50). Although our sample size is larger than that of previous studies using these tests (Andrade et al., 2019; Fernandes et al., 2019a,b), it is important to provide an estimation that covers our outcomes (e.g., BMIs and cotinine).

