#### Study 1—Contrast Sensitivity Function

For the contrast sensitivity analysis, we will use a multivariate analysis of variance (MANOVA), with eight dependent variables (thresholds of each spatial frequency; continuous variables) and one independent, within-subject variable (condition ∼ three levels). *Post hoc* testing will be conducted using discriminant analysis.

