#### Study 2—Cambridge Colour Test

For the Trivector subtest of the CCT, we will use a one-way MANOVA, with three dependent variables (thresholds for protan, deutan, and tritan; continuous variables), and one independent, within-subject variable (condition ∼ three levels). For the Ellipse subtest, we will conduct a separate MANOVA for Ellipse 1 with two dependent variables (angle and area; continuous variables) and one independent, within-subject variable (condition ∼ three dosage). A moderation or mediation analysis (using 5,000 bootstrapping resamples) will be conducted to determine whether the area, length, angle, or ratio is a better predictor of any results of the CCT.

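### The printed 85% power with 42 completers is framed as one sided test with one effect size, so it is unsupported for the planned within-subject MANOVAs

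*Protocol article*

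**What the plan says.** The Sample Size section makes one calculation serve both studies. On effect size, it says that "the effect size will be estimated using the minimal meaningful effect size (0.05"). The test is described as "Considering a two-sided test with an alpha value of 0.01 (or 0.02 for a one-sided test) and a power of 85" per cent, and the result is that "the sample size would require at least 42 individuals to complete the three periods for each study". The section names no statistical test, number of outcomes, standard deviation or correlation.

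The Statistical Analysis section then fixes the tests:

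- Study 1: a "multivariate analysis of variance (MANOVA), with eight dependent variables (thresholds of each spatial frequency; continuous variables"), with condition as a three-level within-subject factor.
- Study 2, Trivector: a "one-way MANOVA, with three dependent variables (thresholds for protan, deutan, and tritan; continuous variables"), with the same factor.
- Study 2, Ellipse: "a separate MANOVA for Ellipse 1 with two dependent variables (angle and area; continuous variables"), with the same factor.

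Outcome Measures makes the 10% criterion for a meaningful difference conditional on a significant main effect or interaction. The outcome of these omnibus tests therefore decides whether that criterion is applied.

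**The concern.** A one- or two-sided test with one effect size describes a single comparison on a single outcome. The planned tests are of another kind. A MANOVA over three conditions asks whether any of several contrasts differs from zero in any direction, so a one-sided version has no meaning. Its power depends on how many outcomes there are, how many of them move, and how they correlate with one another and across conditions. None of this enters the sizing.

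What is at stake is how a non-significant result is read. If the Study 1 MANOVA is null, a reader will set it against the printed 85% and may conclude that a nicotine effect of the planned size has been made unlikely. That inference needs a power figure for the test actually run, and the protocol gives none.

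**Working it through.** **Inputs from the protocol.** Alpha 0.01 two-sided (or 0.02 one-sided), power 85%, effect size 0.05 with no metric named, 42 completers, three conditions, and 8, 3 and 2 dependent variables.

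**1. Can the 42 be reproduced?** Not from the printed inputs in a sided test. For a paired comparison with d = 0.05, n = ((z_alpha + z_power)/d)² gives 5,220 (0.01 two-sided) or 3,820 (0.02 one-sided). Two other readings come near:

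- If 0.05 were meant as d = 0.5, a paired t-test at one-sided 0.02 needs 41 and has 86.5% power at 42. At two-sided 0.01 it needs 56 and has 70% at 42.
- If 0.05 is f² in a repeated-measures ANOVA at alpha 0.01, the sizes are 105, 54 and 34 at between-condition correlation 0, 0.5 and 0.7. So 42 would need an unstated correlation between 0.5 and 0.7, in a test without sides.

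The source of the 42 is therefore undetermined.

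**2. Degrees of freedom.** Three conditions give two contrasts per outcome. In the doubly multivariate form the hypothesis df are q = 2 × 8 = 16, 2 × 3 = 6 and 2 × 2 = 4. The test is Hotelling's T², with F on (q, n − q) df and noncentrality λ = n × D², where D² is the squared multivariate effect. At n = 42 the error df are 26, 36 and 38.

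**3. Noncentrality needed for 85% at n = 42, and power when λ is held at the one-df value.**

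| Test | q | λ for 85%, alpha 0.01 | Power at λ = 14.2, alpha 0.01 | Power at λ = 10.1, alpha 0.04 |
|---|---|---|---|---|
| Single paired contrast | 1 | 14.2 | 85% | 85% |
| Ellipse | 4 | 22.0 | 59% | 62% |
| Trivector | 6 | 26.1 | 48% | 52% |
| Study 1 | 16 | 48.3 | 17% | 25% |

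λ = 14.2 corresponds to d = √(14.2/42) = 0.58. The last column uses two-sided 0.04, the counterpart of one-sided 0.02. A pooled-error Wilks test with λ = 14.2 at alpha 0.01 gives 68%, 59% and 33% for Ellipse, Trivector and Study 1. The drop is therefore not peculiar to T².

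**4. Letting all outcomes shift.** Assumptions, none of them in the protocol: standardised shift d for 4 mg against placebo, d/2 for 2 mg, between-condition correlation 0.5, and a common between-outcome correlation r over p outcomes. Then D² = d² × p/(1 + (p − 1)r).

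For Study 1 with d = 0.5, λ = 42 × 0.25 × 8/(1 + 7r) = 84/(1 + 7r). At alpha 0.01:

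| r | λ | Power |
|---|---|---|
| 0 | 84.0 | 99% |
| 0.3 | 27.1 | 47% |
| 0.5 | 18.7 | 27% |
| 0.7 | 14.2 | 18% |

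Under the same assumptions, Trivector has 93% at r = 0 and 54% at r = 0.5. Ellipse has 83% and 59%.

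**5. Can all three reach 85% together?** Yes. With d = 0.582 on every outcome and r = 0.15, λ is 55.5, 32.8 and 24.7, and power is 91% (Study 1), 94% (Trivector) and 90% (Ellipse). At r = 0.19 the figures are 86%, 92% and 89%. Above about 0.19, Study 1 falls below 85%.

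**The case against.** Three stronger readings are tempting, and the documents support none of them.

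- **That 85% cannot hold for these tests, or for all three at once.** Step 5 is a counter-example.
- **That Study 1 must be the weakest because it has the most outcomes.** With d = 0.5 and uncorrelated outcomes the order reverses: 99% for Study 1, 93% for Trivector, 83% for Ellipse. The ranking needs a fixed total effect or more than weak correlation, and the protocol gives no correlations.
- **That the 42 came from a paired t-test with d = 0.5.** This is inference. No test is named, and the match needs both a changed effect size and the one-sided option.

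The 59%, 48% and 17% also rest on a choice, since they let the extra outcomes add no signal. The between-condition correlation matters too. With d = 0.5 on the raw scale, that correlation at 0.8 and r = 0.3, power is 97%, 100% and 99%, although the single paired test would gain as well. The protocol does not specify the doubly multivariate form, and Outcome Measures lists four ellipse parameters where the analysis names two (four would give 8 df).

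It can also be said that the article never ties the 85% to a MANOVA, that its limitations section admits there is no firm basis for calling the sample large enough, and that detailed power work may sit in a fuller document. All of this limits the claim to unsupported rather than false. It does not remove the mismatch. The article itself prints both the power and the tests, and the limitation neither withdraws the 85% nor says what it applies to. Nor can an equal shift at all frequencies be taken for granted, since the Introduction suggests that high spatial frequencies could be affected more than low ones.

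**Conclusion.** The concern holds in a limited form. The printed 85% with 42 completers describes a sided test with one effect size. The planned tests are omnibus MANOVAs with 16, 6 and 4 hypothesis df, to which sidedness does not apply, and nothing in the protocol carries the figure across to them.

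The size of the gap cannot be fixed from the document. For the same one-comparison effect with nothing added by the other outcomes, power is well short of 85% in all three tests under either test statistic. If every outcome moves, power may lie above or far below 85%, depending mainly on the between-outcome correlation. These illustrations assume multivariate normality, 42 completers with full data, a linear dose pattern and exchangeable correlations. The mismatch itself rests on none of those assumptions.

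**What to change.** Replace the single statement with a power figure for each planned MANOVA (Study 1, Trivector, Ellipse) at the planned number of completers. For each, state the form of the test, the assumed standardised effect per outcome, and the between-outcome and between-condition correlations, with a range. Delete the one-sided option for the omnibus tests.

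Alternatively, keep the 42 and the 85%, name the single comparison and outcome they refer to, and say that they do not establish 85% power for the MANOVAs.

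The cost is a rewritten paragraph and a short calculation. No participants are added. The downside is that the stated power will depend on visible assumptions and will probably look less favourable.

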#### Randomization

Participants will be randomized in accordance with a 1:1:1 permuted block randomization generated by a free resource for researchers^1^. Allocation will be made according to the Cochrane guidelines (Higgins et al., 2019). The main purpose of using a computerized randomization program is to minimize confounding factors and avoid differences between the participants in Study 1 and Study 2 (e.g., similar, or approximately, number of males and females). Fifty participants will be allocated to Study 1, and 50 participants will be allocated to Study 2. All participants will be designated with their initials and a random number by a researcher who is unaware of the condition assignment.

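### Enrolling 50 per study at 20% attrition gives 40 expected completers, two short of the stated minimum of 42, and the 5% missing-data expectation needs reconciling with that attrition

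*Protocol article*

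**What the plan says.** In the protocol article, Sample Size gives the target as a count of completers: "the sample size would require at least 42 individuals to complete the three periods for each study". The power statement behind it is 85% at a two-sided alpha of 0.01, with an effect size of 0.05 whose metric is not named. The enrolment figure follows: "with an anticipated 20% attrition rate, our main intention is to enroll 50 individuals for each study".

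The figure of 50 is not a slip of the pen. Randomization repeats it ("Fifty participants will be allocated to Study 1, and 50 participants will be allocated to Study 2"), and so does Procedures. The article describes no replacement of participants who drop out.

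Safety, Dropouts, and Adherence includes among dropouts anyone who does not complete all of the gum administrations. Additional Analyses treats missing data as missing at random, names maximum likelihood estimation, plans analyses of participants with and without missing data, and adds: "We expect to have no more than 5% of missing data". It does not say whether this is a share of participants, sessions or single measurements, or whether dropouts are included.

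**The concern.** The 42 is a minimum number of people who finish, and the 50 is meant to allow for those who do not. At the article's own attrition rate the allowance falls short, so both studies would be expected to end below the number that the authors say they need. The conclusion depends only on three printed figures (42, 20%, 50), not on how the 42 was obtained.

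The 5% raises a related question. Someone who leaves before finishing three periods has at least one session without data. An expectation of 20% attrition and an expectation of at most 5% missing data can both be true only if they count different things, and the article does not say that they do. A reader cannot tell how much missing data the analysis is expected to carry.

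**Working it through.** **Inputs.** From Sample Size: required completers 42, attrition 20%, enrolment 50, power 85%, two-sided alpha 0.01. From the design: three sessions per participant. From Additional Analyses: missing data at most 5%.

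**Origin of the 50.** The article shows no inflation formula. Multiplying gives 42 × 1.20 = 50.4, close to 50, so this is a plausible origin. It is an inference: 50.4 rounded up would be 51.

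**Enrolment needed.** Required enrolment = completers / (1 − attrition) = 42 / 0.80 = 52.5, rounded up to 53 per study.

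**Completers expected from 50.** 50 × (1 − 0.20) = 40, which is 42 − 40 = 2 short.

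**Attrition that 50 can bear.** 1 − 42/50 = 0.16, or 16%.

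**Chance of reaching 42.** Assume that participants drop out independently with probability 0.20, so that completers are binomial. Then the probability of at least 42 completers is about 31% with 50 enrolled and about 63% with 53.

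**Power (illustrative).** Suppose that 42 completers give exactly 85% power in a paired t-test at two-sided 0.01. The standardised difference that makes this true is 0.581. At that difference, 40 completers give 82.7%. Calibrating a three-level repeated-measures F test to 85% at 42 in the same way gives 82.6% at 40. Either way the loss is about 2 percentage points.

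**The 5% against the 20%.** Attrition of 20% of 50 is 10 people. Sessions planned: 50 × 3 = 150.

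| Each dropout misses | Sessions missing | Share of 150 |
|---|---|---|
| last session only | 10 | 6.7% |
| last two sessions | 20 | 13.3% |
| all three sessions | 30 | 20.0% |

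Five per cent of 150 is 7.5 sessions, fewer than the 10 lost in the mildest case. Counted by participant, 5% of 50 is 2.5 people against 10. So if dropouts count as missing data, no pattern of stopping brings 20% attrition within 5%. If the 5% covers only gaps among the 40 who stay, the two statements are compatible.

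**The case against.** The strongest objection is that this hardly matters. Two completers and about two points of power are well inside the uncertainty of any sample size calculation. Strengths and Limitations already concedes that there is no firm basis for calling the sample large enough, and maximum likelihood could recover some information from those who stop early. All of this stands, and it sets the severity at minor. It does not make 50 less 20% equal to 42, and the criterion that the article sets is completers.

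Four stronger readings might be inferred, and the document does not support them.

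- *That 5% flatly contradicts 20%.* One is participant attrition used for recruitment; the other is missing data with no unit given. They conflict only if dropouts are counted in the 5%.
- *That the missing-data method rests on the 5%.* Additional Analyses justifies maximum likelihood by the missing-at-random assumption. The 5% is a separate expectation and carries no part of that argument.
- *That 20% should simply replace 5%.* This would mix units. Twenty per cent of sessions are lost only if every dropout misses all three.
- *That the plan has a detectable standardised difference of about 0.58, or 0.60 with 40 completers.* Such values are solved backwards from 42 under a paired t-test. The planned analyses are MANOVAs, and the stated effect size is 0.05 in an unnamed metric.

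**Conclusion.** The enrolment figure is wrong on the article's own terms: 50 at 20% attrition yields 40 expected completers, not 42. This holds however the 42 was derived, and assumes only that 50 is the number enrolled and that dropouts are not replaced. The practical loss is about 85% to 83% power under the illustrative paired t-test, so the point is a minor correction and does not show that the studies are materially underpowered.

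The 5% expectation is ambiguous. It is incompatible with 20% attrition if dropouts count, and compatible if it describes gaps among retained participants. Multiplying by 1.20 remains a likely explanation of the 50, not an established one.

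**What to change.** **Sample Size.** Keep 50 per study and make the figures agree, in one of two ways:

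- state that 40 completers are expected at 20% attrition, slightly below the minimum of 42, with power of about 83% if 42 gives 85%. Label that power figure as illustrative and as assuming a paired t-test at two-sided 0.01;
- or state that enrolling 50 meets the minimum of 42 for attrition up to 16%.

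Do not add a detectable standardised difference of 0.60 as if it were the plan's own figure.

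**Additional Analyses.** Reconcile the 5% with the attrition rate, either by saying that it covers only gaps among retained participants, or by replacing it with the session-level missingness that 20% dropout implies: 6.7% to 20%, depending on when participants stop.

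**Cost.** A sentence in each section. Enrolment, design and planned models stay as they are, and the claimed power becomes slightly less favourable. Holding to 42 at 20% attrition would instead take 53 per study, 106 in total, which is six more participants; the size of the shortfall does not make that necessary.
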